### Intervention

Two groups will be formed: a study group and an active control group. The study group will receive dextroketamine chloralhydrate IM (0.75 mg/kg) plus 2 placebo tablets orally, one in the morning and the other at night. The active control group will receive saline solution IM plus one of the alternative therapies for TRD: escitalopram 15 mg (morning) or aripiprazole 5 mg (night) (10). Injections will be applied alternately to gluteal muscles in the external upper quadrants. For 4 weeks (1 month), applications will be applied on Mondays, Wednesdays, and Fridays (giving a total of 12 interventions). For the ensuing 6 months, applications will be weekly (giving a total of 24 interventions). For 4 weeks (1 month), participants will continue to receive the tablets (active treatment or placebo) and be monitored. Safety parameters: vital signs will be monitored continuously by the researchers for 2 h post-application: fingertip pulse oximetry, heart rate, breathing rate, blood pressure, and electrocardiography. Abnormal blood pressure will be defined as low <90/60 mmHg and high >140/90 mmHg. Abnormal heart rate will be defined as <60 or >100 bpm. Abnormal breathing rate will be defined as <10 cycles/min or >20 cycles/min. Low oxygen saturation will be defined as levels <95%. Collateral symptoms such as nausea and vomiting will be managed using ondansetron 8 mg sublingually (SL). Individuals presenting episodes of anxiety, hallucinations, or intense dissociative effects will be given clonazepam SL 0.25 mg. An emergency team will be deployed in the event of serious acute events such as heart arrhythmia or prolonged hypertension. Patients will be placed under observation in a quiet comfortable environment and will be cleared to leave after 2 h, accompanied by a competent adult.

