The safety of ketamine has been confirmed for some decades, with anesthetic doses of 4–5 mg/kg intramuscularly (IM) proving effective [93–100% of children (1,022 pediatric cases)] for airways, emesis, or agitation (46). In a small number of patients, the drug can temporarily affect heart rate, and blood pressure and promote myocardial ischemia, although these risks can be attenuated by the use of sub-anesthetic doses and careful patient selection (27, 41, 44, 47). Dissociative states, a common side effect of the drug, are transient (lasting ~40 min, 2 h after use) and are not associated with persistent psychosis or mood swings (48). Of 158 patients given ketamine, 21 (13.3%) withdrew from the study, compared to 10 (7.4%) out of the 135 patients receiving control interventions (OR 1.95, 95%CI 0.86–4.42, *z* = 1.59, *p* = 0.11) (39). Claims that NMDA receptor blocking can cause “brain damage” and that ketamine affects the urinary retract remain the subject of controversy (49). The most common (≥20%) adverse events following the use of the drug include, headache, anxiety, dissociation, nausea, dizziness, and drowsiness on days of the administration, with these effects dissipating within 2 h, while more serious side effects leading to hospitalization or suicide attempts are rare (40, 50, 51). Anti-depressant effects of ketamine are short-lived (days or weeks), although longer-term benefits can be maintained by use of repeat doses, warranting further studies on the prolonged effects of the drug (44, 52). Intranasal (IN) esketamine was approved for use in 2019 by both the U.S. Food and Drug Administration (FDA) and the European Medicines Agency (EMA) (53). Other administration routes have also been investigated: IN, subcutaneous (SC), and oral (54–56).

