### Inclusion and exclusion criteria

**The following individuals will be eligible for study inclusion:** Subjects residing in Itajaí valley (Santa Catarina state, Brazil); adults (age 18–40 years) with a primary diagnosis of TRD based on clinical evaluation and confirmed by the SCID-IV [research version (TRD defined as failure of 2–5 clinical trials with anti-depressants including ECT)]; moderate-severe intensity disease [clinical criteria and/or score ≥14 on the Hamilton Depression Rating Scale (17-item HAM-D)]; with no psychotic symptoms; not presenting an imminent risk of suicide (as indicated by clinical evaluation and HAM-D) and/or murder; with anxiety disorders (secondary); with compensated clinical comorbidities and; literate and able to understand the tasks requested (69). Patients and/or legal guardians must be aware of the nature of the study and give consent by signing the Free and Informed Consent form. All patients will undergo a physical and neurological examination, laboratory tests, and an electrocardiogram (ECG) to ascertain their comorbid clinical and/or uncompensated conditions. **The following individuals will be excluded from the study:** Subjects exhibiting imminent risk of suicide, presenting bipolar spectrum disorders or other diagnosed psychiatric conditions (primary); psychoactive substance dependence within the last year; intellectual deficit; allergy to ketamine; and glaucoma. Fertile women must be in use of a clinically acceptable method of birth control [oral contraceptive and/or condom (only unfollowed topic in GCP)]. In the event of clinical doubt regarding pregnancy, a test for beta-human chorionic gonadotropin (βHCG) hormone will be ordered. Patients who become pregnant during the study period will be excluded and referred for obstetric care. The medication wash-out period required before visit 0 will be 1 week for antipsychotics, antidepressants [except fluoxetine (4 weeks)], and for mood stabilizers. No other medications with psychiatric action will be allowed during the study, except for Lorazepam and Zolpidem for patients in the use of a benzodiazepine or hypnotic agent.

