### Measures and outcome variables

The study will assess (given in Table 1):

Sociodemographic variables: gender, marital status, ethnicity, number of children, income, education, and employment.Clinical characteristics over the life course: clinical and psychiatric comorbidities, smoking, family history of mood disorders, prior pharmacological treatment and ECT, number of mood episodes, previous psychiatric admissions, suicide attempts, currently receiving psychotherapy, and history of sexual, or physical abuse.Clinical history: visits to the emergency room, attempted suicides, or psychiatric hospitalizations.The Montgomery-Åsberg Depression Rating Scale (MADRS) (70, 71): will be applied as a primary outcome measure 3× per week for the first month (PII), 1× per week for 6 months (PIII), and 1× per week (PIV) for 1 month.The Hamilton Rating Scale for Depression (HAM-D) (72, 73): will be applied once in PI to assess symptom severity and again 3× per week for 1 month (PII), 1× per week for 6 months (PIII), and 1× per week (PIV) for 1 month.Vital signs (VS): pulse oximetry, heart monitoring, breathing rate, heart rate, and blood pressure will be checked continuously using non-invasive methods. VS to be monitored 3× per week for the 1st month (PII) and 1× week (PIII) for 2 h continuously after completion of each application.Global Clinical Impression (GCI) scale: this will be applied 3× a week for 1 month (PII), 1× week for 6 months (PIII), and 1× week (PIV) to assess disease severity, global improvement of the condition and hence, treatment efficacy (74).Depression Thoughts Scale (DTS): the DTS will be applied at visit one (V-1), V11, and V-39 to assess for thought distortions (75, 76).Clinician-Administered Dissociative States Scale (CADSS): this will provide a measure of the dissociative effects of ketamine and will be applied 3× per week for the 1st month (PII), and 1× per week for 6 months (PIII), ~1 h after application of injections (77).Young's Mania Rating Scale (YMRS): this scale will be employed in this study to assess manic switching as an adverse effect of the medications and applied 3× week for the 1st month (PII) and 1× week for 6 months (PIII), ~1 h after application of injections (78).Brief Psychiatric Rating Scale (BPRS): Sub-item 12 of the scale will be used for detecting the presence of psychotic symptoms arising after application of ketamine, applied 3× week for 1 month (PII) and 1× week (PIII), ~1 h after application of injections (79).Udvalg Kliniske Undersoegelser Side Effect Rating Scale (UKU-SERS): this will be used to determine the presence of side effects of the medications used and will be applied 3× week for the 1st month (PII) and 1× week (PIII) thereafter, around 1 h after application of injections (79).World Health Organization Quality of Life, brief version (WHOQOL-Bref): this scale will be applied at V-1, V-11, and V-35 (80).Sheehan Disability Scale (SDS): this scale will be applied at V-1, V-11, and V-35 (81).

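### The eligibility section bars clonazepam throughout the study while the Intervention section requires it for acute symptoms; the two must be reconciled, and its timing recorded against the 1 h tolerability ratings

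*Protocol article*

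**What the plan says.** Two sections of the protocol article govern psychiatric drugs given during the trial.

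- **Inclusion and exclusion criteria**, after the wash-out rule: "No other medications with psychiatric action will be allowed during the study, except for Lorazepam and Zolpidem". The exception is narrowed at once: it applies "for patients in the use of a benzodiazepine or hypnotic agent".
- **Intervention**, among the safety measures after injection: "Individuals presenting episodes of anxiety, hallucinations, or intense dissociative effects will be given clonazepam SL 0.25 mg". No arm is named and there is no restriction to prior benzodiazepine users.

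The Measures and outcome variables section then lists the tolerability ratings. Of CADSS it says: "this will provide a measure of the dissociative effects of ketamine". Sub-item 12 of the BPRS is used for "detecting the presence of psychotic symptoms arising after application of ketamine". CADSS, BPRS item 12, YMRS and UKU-SERS are all placed about 1 h after the injection. The Intervention section keeps patients under observation for 2 h.

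**The concern.** The list of permitted drugs is closed, and clonazepam is not on it. Yet another section says that patients with certain symptoms will receive it. Staff at the site and whoever classifies deviations need a single rule, and the article gives two.

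The conflict also touches a stated objective. Safety and tolerability are named under Study hypotheses, and the symptoms that trigger clonazepam overlap with those that CADSS and BPRS item 12 are there to measure. If the drug is sometimes given before the 1 h rating, the score from that visit describes a treated patient. If use also differs between the arms, the tolerability comparison may look more favourable than it should for the arm with more use.

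**Working it through.** No figure in the plan is in dispute and there is none to reproduce. The check sets the sections side by side.

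**Step 1: do the two rules conflict?** Take a patient with intense dissociation after an injection.

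| Patient | Inclusion and exclusion criteria | Intervention |
|---|---|---|
| Not using a benzodiazepine or hypnotic | No psychiatric drug allowed | Clonazepam given |
| Already using one | Lorazepam or zolpidem only | Clonazepam given |

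The sections disagree for both kinds of patient. The anti-nausea drug named in the same paragraph of the Intervention section raises no such problem, because it is not given for a psychiatric effect. Clonazepam is given for exactly that.

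**Step 2: can clonazepam precede the ratings?** The observation period runs from 0 to 2 h after injection and the four ratings fall at about 1 h. The Introduction says of the drug: "Dissociative states, a common side effect of the drug, are transient", with a duration of roughly 40 minutes, and says that the common adverse effects clear within 2 h. Symptoms that call for clonazepam can therefore arise before or after the rating. Both orders are possible, and the article does not fix which applies.

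**Step 3: how often could this arise?** The Intervention section gives 12 injections in the acute phase and 24 in maintenance, so 12 + 24 = 36 occasions for a patient who completes both. The article gives no rate of clonazepam use per injection or per patient, so no expected number of affected ratings can be calculated.

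**Step 4: is use likely to be uneven?** There are three triggers: anxiety, hallucinations and intense dissociation. The Introduction lists two of them, anxiety and dissociation, among adverse events seen in at least 20% on dosing days; hallucinations are not in that list. The control injection is saline. This points to more use under ketamine. Against that, the clonazepam provision covers both arms, and the eligibility criteria admit patients with secondary anxiety disorders to either.

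**Step 5: would it reach the analysis?** The Statistical analysis section applies the between-arm repeated-measures ANOVA to the main outcome and the other scales. If CADSS, YMRS or similar scores are analysed that way, any rating lowered by clonazepam enters the comparison unmarked.

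**The case against.** The strongest reply is that the two rules concern different things. The eligibility rule stands beside the wash-out requirement, and its exception is for patients already on a sedative, which suggests background medication. The Intervention provision covers acute events under observation, and a site would probably treat it as the specific rule. That reading is sensible, but the article does not state it: the prohibition applies to the whole study without qualification, and neither section mentions the other. This is not detail left to a fuller document, since both rules are printed and they disagree.

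Other objections succeed against stronger readings that a reader might be tempted to draw:

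- **That use falls almost wholly in the ketamine arm.** The provision names no arm, anxiety is a trigger, and anxiety disorders are admitted in both. Higher use under ketamine is plausible; near-zero use under saline is not documented.
- **That clonazepam blunts the ratings.** The article sets no order between drug and rating and gives no effect of this dose on any scale. Dissociation is described as brief, so a 1 h rating could miss its peak even without clonazepam.
- **That the primary outcome is biased.** MADRS has no stated time relative to the injection. If it is rated beforehand, clonazepam given later that day cannot affect that score.
- **That most ketamine patients would be treated at least once over 36 injections.** This needs an assumed rate per injection and independence between injections. The article gives no rate, and use would be expected to cluster in susceptible patients. Severe psychotic symptoms and intolerance are also grounds for withdrawal, so some of the worst-affected patients would not reach 36.

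Finally, recording times and reporting use by arm are normally matters for the case-report form or analysis plan. Their absence from the article is not counted as a fault here; they are part of the remedy for the contradiction.

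**Conclusion.** The contradiction is definite and rests on wording alone: the same clonazepam dose is barred by the Inclusion and exclusion criteria and required by the Intervention section. Its status as a deviation is undefined. The passages must be reconciled; which rule is right is a clinical matter on which this review takes no position.

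The consequence for the tolerability ratings is a possibility, not a demonstrated bias. It requires that clonazepam is sometimes given before the 1 h rating, that it lowers the score, and, for a distorted comparison, that use differs between arms. The article makes the first possible and the third likely, and it is silent on the second. No size can be attached to it. Nothing in the document supports extending the point to MADRS.

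The point deserves correction because it concerns a stated objective and is cheap to settle. It does not threaten the primary comparison.

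**What to change.** 1. Reconcile the Inclusion and exclusion criteria with the Intervention section, so that one rule says which psychiatric drugs may be given during the study and to whom. State whether clonazepam given for acute symptoms counts as a protocol deviation.
2. Record each use with its clock time, so that it can be placed before or after the 1 h CADSS, BPRS item 12, YMRS and UKU-SERS ratings.
3. Report use by arm as a tolerability outcome beside CADSS and BPRS, and flag ratings made after clonazepam.

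Two further steps may suggest themselves and are better avoided. Rating only treated patients on their worst earlier state would create two measurement rules that may divide by arm. Setting aside MADRS scores from days of use would remove data on a post-randomisation event, which sits badly with the stated intention-to-treat analysis.

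The cost is a wording change and one case-report-form field. Ketamine's reported tolerability may look slightly worse. The article says the study is already under way, and times not recorded now may not be recoverable later.

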### Blinding

The researchers performing the clinical monitoring and application of the outcomes will be blinded, and the study participants will also be blinded. A nurse, not involved in data collection, will distribute the medications and apply the injections according to the randomization process.

### Sample size calculation

The sample size was calculated based on a similarly designed RCT (45). Assuming a statistical power of 90% with a clinically significant minimum effect of 0.5 (Cohen's d) and alpha 5%, a total of 88 subjects will be needed (44 in the EG and 44 in the CG). Given this is a long-duration study, a drop-out rate of 10–20% was estimated.

### Statistical analysis

All analyzes will be performed using the Statistical Package for the Social Sciences-SPSS® (82). Specific and sociodemographic variables will be expressed generally and between intervention groups in relative and absolute frequencies, means, medians, standard deviation, and 95% confidence interval. Continuous variables will be evaluated by the *T*-student or U-Mann Whitney-test according to their distribution and the qualitative ones by the *X*^2^-test. The distribution of variables will be evaluated using the Shapiro Wilk. The global significance level adopted is 0.05. To determine the effects of intervention throughout the study (main outcome and other scales), repeated measures ANOVA (two-way) will be applied, considering the temporal effect of visits (v-0 to v-final) and the intervention effect (EG × CG). In identifying the significant interaction effect, one-way repeated measures ANOVA test or its non-parametric alternative (Friedmann test) will be performed to verify that the effect is independent of treatment. Contingency tables and *X*^2^-tests will be applied to compare responders and non-responders in the intervention groups. Analysis using intent-to-treat (ITT) will be employed to assess the results (83). Vital signs will be assessed using two repeated measures ANOVA (two-way). First, considering the effect of the intervention immediately (3 evaluations at each visit) and the second, evaluating the effect of the intervention on VS over time (acute and maintenance treatment).

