## Methods

### Design and study populations

A comparative, parallel-group, randomized, double-blind trial is to be conducted involving an anti-depressant intervention. The experimental group (EG) will use the experimental substance [ketamine IM 0.75 mg/kg, oral placebo (morning), and oral placebo (evening)], while the control group (CG) will use an active treatment administered orally [escitalopram 15 mg (morning), aripiprazole 5 mg (evening) and placebo IM]. The study will be carried out by the Institute of Psychiatry of the University of São Paulo Medical School (HCFMUSP), in conjunction with the Center for Mind Health Studies (NUPE) in the Vale do Itajaí, Santa Catarina state, Brazil. The study is called the KETAMIM project and is Registered Under No. NCT04234776 on the www.ClinicalTrials.gov platform. The study phases and methodological aspects comply with the recommendations of the CONSORT (Consolidated Standard of Reporting Trials) statement and with Good Clinical Practice guidelines (GCP) (65, 66). The study is in running.

The study shall entail 5 phases: (1) Dissemination (P0): patients referred by health professionals, dissemination in the press or online media; (2) Pre-treatment (PI): ~2 weeks for the baseline assessment of candidates for study entry; (3) Therapeutic trial (PII): 4 weeks for ketamine use 3 times weekly and of daily oral medications, as well as placebos for both groups, characterizing acute treatment of the disease; (4) Maintenance (PIII): 24 weeks for weekly ketamine use and maintenance of standard treatment and respective placebos; (5) Post-treatment (PIV): 4 weeks for assessing patients after use of ketamine, maintenance oral medication or placebo.

A total of 88 patients with TRD (≥2 failed trials using anti-depressants, plus ECT as an alternative or otherwise) of moderate-severe intensity [according to criteria of Diagnostic and Statistical Manual of Mental Disorders (DSM-5)], and the diagnosis confirmed by the Portuguese version of the clinical interview of the DSM-IV, will be recruited (67). Patients will be block randomized using a computer-generated list into one of the two interventions (1:1 ratio), EG or CG (68). A nurse blinded to the allocation will administer ketamine or saline IM, placebo orally, or the active treatment, respectively.

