### Reasons for withdrawal or termination

Subjects who meet one or more of the criteria outlined below will be withdrawn from the study:

Intolerance to medications;Abnormal results on lab tests;Serious adverse event;The above-mentioned items will be assessed individually by the team according to medical criteria. Prolonged arterial hypertension, serious allergies, abnormal heart rate, or worsening of pre-existing diseases, among others, will be checked. Manic switching, imminent risk of suicide, attempted suicide, severe psychotic symptoms, aggressiveness, etc. will constitute grounds for study withdrawal.Relapse or lack of response in Phases II or III. Lack of response will be defined as reduction or maintenance of scores on the index scale of ≤25%, whereas relapse will be the attainment of scores <50% in individuals who had achieved remission or response during the study.Two consecutive visits missed;Withdrawal of consent for the study.

Patients who discontinue the study shall be given guidance to continue outpatient psychiatric treatment.

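### The repeated-measures ANOVA over all visits needs a complete row of about 40 ratings per patient, so as written it drops randomised patients in a way tied to outcome and does not deliver the promised ITT analysis

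*Protocol article*

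**What the plan says.** The Statistical analysis section fixes the method for the main outcome and the other scales: "repeated measures ANOVA (two-way) will be applied, considering the temporal effect of visits (v-0 to v-final"), crossed with the intervention effect. On software: "All analyzes will be performed using the Statistical Package for the Social Sciences-SPSS". On the analysis population: "Analysis using intent-to-treat (ITT) will be employed to assess the results". The section gives no rule for missing ratings.

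The number of ratings follows from three other sections:

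- Measures and outcome variables: the MADRS "will be applied as a primary outcome measure 3× per week for the first month (PII), 1× per week for 6 months (PIII"), then weekly for one month in PIV.
- Intervention: in the acute phase "applications will be applied on Mondays, Wednesdays, and Fridays (giving a total of 12 interventions"); in maintenance "applications will be weekly (giving a total of 24 interventions").
- Design and study populations: "Post-treatment (PIV): 4 weeks for assessing patients after use of ketamine".

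The Sample size calculation section sets 88 patients (44 per arm) for 90% power at d = 0.5 and alpha 5%, and expects 10–20% drop-out. Reasons for withdrawal or termination takes patients out of the study for relapse or lack of response in Phases II or III, for intolerance and serious adverse events, and for "Two consecutive visits missed". Afterwards it describes only guidance towards outpatient care. It mentions no further ratings.

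**The concern.** In its usual form, including the SPSS repeated-measures procedure, this ANOVA treats each visit as a column and omits any patient with an empty column. One gap among about 40 ratings removes all of that patient's data.

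Two kinds of gap follow from the article's own rules. Withdrawn patients have no later ratings, and some are withdrawn because of their scores. Patients who miss one visit stay in the study, because only two misses in a row trigger withdrawal, but they too have an incomplete row.

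The first kind is the more serious. If non-responders and relapsers leave the analysis, the comparison is between patients selected on the outcome being compared, possibly at different rates in the two arms. That is no longer the randomised comparison, and it conflicts with the ITT statement in the same section. The second kind mainly costs precision.

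**Working it through.** **1. Number of ratings.** PII 12 + PIII 24 + PIV 4 = 40, plus any separate baseline rating.

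**2. The plan's own figure of 88.** A two-sided two-sample comparison at one time point (d = 0.5, alpha 5%, power 90%) needs 85 per arm, 170 in all, so it does not give 88. A comparison of 40-visit averages can. With an assumed common correlation ρ = 0.5, the variance of a patient's average is (1 + 39 × 0.5)/40 = 0.5125 of the single-visit variance. The effective standardised difference is then 0.5/√0.5125 = 0.698, which needs 44 per arm. The article states neither the correlation nor this formula, and a one-sample test at the same settings also gives 44, so the origin of 88 remains unknown.

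**3. Complete rows.** Expected count = 88 × (1 − drop-out) × (1 − m)^40, where m is the chance that a retained patient misses a given visit, independently of other visits. Drop-out is from the article; m is an assumption.

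| m | (1 − m)^40 | 10% drop-out | 20% drop-out |
|---|---|---|---|
| 0 (article's drop-out only) | 1 | 79 | 70 |
| 0.5% | 0.818 | 65 | 58 |
| 1% | 0.669 | 53 | 47 |
| 2% | 0.446 | 35 | 31 |

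**4. Power for the between-arm 40-visit average** (d = 0.5, two-sided 5%, t-test on patient averages, effective difference as in step 2):

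| Complete rows | ρ = 0.3 | ρ = 0.5 | ρ = 0.7 |
|---|---|---|---|
| 88 | 98% | 90% | 79% |
| 79 / 70 (stated drop-out) | 97% / 96% | 87% / 82% | 74% / 69% |
| 53 / 47 (1% missed as well) | 89% / 85% | 70% / 65% | 56% / 51% |

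The effective differences at ρ = 0.3 and 0.7 are 0.5/√0.3175 = 0.887 and 0.5/√0.7075 = 0.594.

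**5. Selection on response (illustration only).** The Introduction reports MADRS changes in the trial on which the sample size was based: −18.4 (SD 12.0) on twice-weekly ketamine and −5.7 (SD 10.2) on placebo, a difference of 12.7 points. Assume normal changes and a baseline MADRS of 28 to 36, and remove everyone whose score falls by 25% or less. Then 78–83% of the ketamine arm and 37–45% of the comparator arm stay, 51 to 56 of 88 patients. The difference among those who stay is about 7 points. That comparator was placebo and this trial's is active, so the calculation shows direction and possible scale. It is not a forecast.

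**The case against.** The strongest reply is that the article names SPSS but no procedure, and is a condensed report. Ratings could be imputed before the ANOVA under a fuller plan that is not shown, and all 88 patients would then be analysed. This stands as a limit: silence on imputation is not the fault, and the conclusion applies to the analysis as written. It does not remove the point, because the article itself pairs a method that needs complete rows with rules that produce incomplete ones, and promises ITT.

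Some stronger readings are tempting but not supported:

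- *A reader might infer that only a small remnant of patients would be analysed.* The only loss the article states leaves 70–79 of 88. Counts in the thirties need an assumed 2% of visits missed on top of drop-out.
- *A reader might quote the low power of a single-visit comparison.* That is not the named test, and its power is only about 64% at the full 88, so most of that shortfall does not come from deleting incomplete rows.
- *A reader might object that sphericity cannot hold over unevenly spaced visits.* In null simulations of this schedule, the Greenhouse–Geisser correction kept the interaction test's type I error at 4–5%. The article does not choose the uncorrected result.
- *A reader might infer that a pre-treatment rating is wrongly modelled as an outcome.* The article does not say that the V-0 MADRS precedes the first injection, and Table 1 marks no MADRS at baseline. Under randomisation, a group-by-time test that includes a baseline would still be valid.

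**Conclusion.** The conflict holds. As written and without imputation, the primary analysis excludes randomised patients, partly because of their outcome, and does not deliver ITT. This part needs no assumed figure: it follows from the named method, the expected drop-out and the withdrawal rules.

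The size is less certain. The stated drop-out alone costs 9 to 18 patients (88 − 79 and 88 − 70) and takes power for a 40-visit average from about 90% to 82–87% at ρ = 0.5. Larger losses, such as 65–70% power with 1% of visits missed as well, depend on an assumed miss rate, independence between visits and the assumed correlation. The bias from selection on response cannot be quantified for this active comparator, but it bears on validity at least as much as the lost rows bear on precision.

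**What to change.** Replace the repeated-measures ANOVA as primary analysis with a likelihood-based linear mixed model (SPSS MIXED, REML) on all randomised patients and all observed MADRS ratings.

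- Fixed effects: arm, visit (or week) and arm × visit.
- Covariates: a pre-treatment severity score (the pre-injection MADRS if one is taken, otherwise the baseline HAM-D) and any stratification factor used at randomisation.
- Fixed in advance: the covariance structure, and the time point or average at which the EG–CG difference and its 95% confidence interval are reported.
- Sensitivity analysis: a range of assumptions under which ratings after withdrawal are missing not at random.

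The model uses every recorded rating and stays valid when drop-out depends on scores already recorded, which largely describes withdrawal for non-response or relapse. It does not recover outcomes after a patient leaves the study, hence the sensitivity analysis. No change to the withdrawal rules is proposed.

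The cost is a change of wording before unblinding, with the same software and data. The downside is that the covariance structure and the contrast must be committed to in advance.
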